#### Specific Aim 1: Are Ambulatory Measures of Subjective and Objective Cognitive Function More Sensitive to Longitudinal Changes in Cognitive Function Compared With Conventional Clinic-Based Assessments?

Nonparametric tests (Wilcoxon signed rank test, 2-tailed) will be used to compare cognitive test scores (ambulatory vs clinic-based measures) for each participant at each time point. We will test whether the proportion of cases where the ambulatory test indicates a greater degree of cognitive decline compared to the clinic-based cognitive tests is statistically different from 0. Additional sensitivity tests of the paired differences in proportions of 4 categories (no decline, absolute but subtle decline, meaningful decline, or clinically significant decline) for each cognitive domain between ambulatory and clinic-based neurocognitive tests at both 1- and 2-year follow-up will be conducted [80]. Mixed effects models will be used to examine changes over time for each cognitive measure, with the expectation that the ambulatory measures will show larger time effects at both 1- and 2-year follow-up.

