**Methods:**

Participants—ambulatory adults with medically documented MS—are assessed over the course of 2 years on an annual basis (3 assessments: T1, T2, and T3). A comprehensive survey battery, in-laboratory cognitive and physical performance tests, and 14 days of ambulatory data collection are completed at each annual assessment. The 14-day ambulatory data collection includes continuous wrist-worn accelerometry (to measure daytime activity and sleep); ecological momentary assessments (real-time self-report) of somatic symptoms, mood, and contextual factors; and 2 brief, validated cognitive tests, administered by smartphone app 4 times per day. Our aim was to recruit 250 participants. To ensure standard test protocol administration, all examiners passed a rigorous examiner certification process. Planned analyses include (1) nonparametric 2-tailed *t* tests to compare in-person to ambulatory cognitive test scores; (2) mixed effects models to examine cognitive changes over time; (3) mixed effects multilevel models to evaluate whether ambulatory measures of physical activity, sleep, fatigue, pain, mood, and stress predict changes in objective or subjective measures of cognitive functioning; and (4) mixed effects multilevel models to examine whether ambulatory measures of cognitive functioning predict social and physical functioning over short (within-day) and long (over years) time frames.

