Using these innovative assessment methods, we aim to explore foundational questions that have yet to be examined in MS, such as the degree and prognostic utility of within-person lability in cognitive function. We will determine if ambulatory assessments are sensitive to subtle declines in cognitive functioning. We will also explore the impact of modifiable factors, such as sleep, physical activity, mood, and somatic symptoms on cognitive function. Finally, we will explore whether variability in cognitive functioning predicts short- and long-term changes in other patient-centered functional domains, social participation, and physical functioning. In pursuit of these primary objectives, the study is designed to test three hypotheses: (1) ambulatory measures of subjective and objective cognitive function will be more sensitive to longitudinal changes (over 2 years) in cognitive functioning compared to conventional clinic-based assessments; (2) ambulatory measures of modifiable factors—physical activity, sleep, fatigue, pain, mood, and stress—predict short-term (same-day) and long-term (at 1- and 2-year follow-up) changes in cognitive functioning; and (3) ambulatory measures of cognitive functioning will predict social and physical functioning over short- (same-day) and long-term (at 1- and 2-year follow-up) time frames.

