**Physical activity (via ActiGraph accelerometer)**			
	Daytime physical activity and nighttime sleep activity	Continuous for 24 hours	

^a^All time points except morning.

Two brief, valid, and reliable cognitive tests [13] are administered via the smartphone app. Response time speed is recorded in milliseconds for all tests. The Symbol Search Test (Figure 3) is a test of processing speed. Participants see a 2x2 grid of 4 symbol pairs at the top of the screen and are presented with 2 symbol pairs at the bottom of the screen. Stimuli are presented until a response is provided. Participants decide, as quickly as possible, which symbol pair at the bottom matches one of the symbol pairs at the top and select the matching pair by touching their selection at the bottom. In total, 24 trials are administered for each session. Reaction time and errors are recorded for sessions where effort is deemed adequate (accuracy >70%).

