**Figure 3 figure3:**
[figure not shown]
(A) Symbol Search landing page, (B and C) test instructions, and examples of (D) a “nonlure trial” (where neither symbol in the incorrect pair on the bottom appears in the pairs above) and (E) a “lure trial” (where one of the symbols in the incorrect pair on the bottom appears in a pair above).

The Dot Memory Test (Figure 4) is a test of working memory. Each trial consists of 3 phases: encoding, distraction, and retrieval. During the encoding phase, the participant is asked to remember the location of 3 red dots appearing on a 5×5 square grid. After a 3-second study period, the grid is removed, and the distraction phase begins, during which the participant is required to locate and touch the F’s in an array of E’s. After performing the distraction task, an empty 5×5 square grid is presented, and the participant must place the red dots (by touching the empty squares) in the correct locations. Participants press “Done” when they are finished. Speed and Euclidean distance (a score of the collective distance of the 3 dots from their correct locations) are recorded. In total, 4 trials are administered for each session.

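### The Aim 1 Wilcoxon test compares score levels of different instruments at each visit, with no common metric stated, while hypothesis 1 is about change

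*Protocol article*

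**What the plan says.** Hypothesis 1 (Introduction) is that ambulatory measures "will be more sensitive to longitudinal changes (over 2 years) in cognitive functioning compared to conventional clinic-based assessments". The target is therefore change, compared between two kinds of instrument.

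Under Data Analysis, Specific Aim 1, the first analysis named is "Nonparametric tests (Wilcoxon signed rank test, 2-tailed"), and these tests "will be used to compare cognitive test scores (ambulatory vs clinic-based measures) for each participant at each time point". The abstract keeps this apart from the analysis of change. Its item (1) is a test "to compare in-person to ambulatory cognitive test scores; (2) mixed effects models to examine cognitive changes over time".

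On the ambulatory side, "Response time speed is recorded in milliseconds for all tests". Symbol Search yields reaction time and errors. For Dot Memory, "Speed and Euclidean distance (a score of the collective distance of the 3 dots from their correct locations) are recorded". The clinic side consists of different instruments: the oral Symbol Digit Modalities Test, the Paced Auditory Serial Addition Test, the Rey Auditory Verbal Learning Test, the ReacStick Test and the NIH Toolbox battery. The article does not give their scoring units or direction.

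Specific Aim 1 also plans a test of whether the proportion with greater ambulatory decline differs from zero, paired comparisons of four decline categories at both follow-ups, and mixed models over time for each measure. The decline categories are defined in SD units under Sample Size Analyses. No scaling is stated for the Wilcoxon test.

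**The concern.** A signed rank test ranks within-pair differences, so the two members of a pair must be on one scale for the difference to mean anything. A reaction time in milliseconds minus a score from another test has no such meaning. Even on a common scale, a difference between instruments at one visit is a difference in level. At T1 there is no elapsed time, so the result cannot bear on decline.

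The risk is that a planned analysis, listed first in the abstract, yields a very small p value or a null that is then read as evidence for or against hypothesis 1. Depending on the scaling chosen later, it may reflect only units, only the standardisation, or a mismatch in score direction.

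**Working it through.** **1. The plan's own Aim 1 figure.** The inputs, from Sample Size Analyses, are n = 199, a proportion of 1.5% and 95% power. The figure reproduces as the chance of at least one such case: 1 − (1 − 0.015)^199 = 0.9506. With n = 198 it is 0.9498, so 199 is the smallest n that reaches 95%. This sizes the proportion test. No sample size is stated for the Wilcoxon test.

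**2. What the Wilcoxon test compares.** Let A be the ambulatory score and C the clinic score of one participant at visit t. As worded, the test uses A(t) − C(t). Hypothesis 1 needs [A(t) − A(1)] − [C(t) − C(1)] on a common scale. At t = 1 the first quantity contains no follow-up data.

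**3. Raw scores.** If the scales do not overlap, all n differences share a sign and W = 0. For n = 210, the expected final sample:

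- mean of W under the null = 210 × 211 / 4 = 11,077.5
- SD = √(210 × 211 × 421 / 24) = 881.6
- z = 11,077.5 / 881.6 = 12.57, so two-sided p = 3.3e-36

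Any 210 same-sign pairs give this value. In a generated data set, W and p were identical before and after a constant was added to the ambulatory scores. A distance near 3 set against a score near 50 also gave W = 0.

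**4. Simulation under different scalings.** There were 210 pairs, two-sided alpha .01 and 1000 runs per scenario. Assumptions not in the documents: normal scores; reaction time mean 2500 ms, SD 700; clinic score mean 50, SD 12, higher better; correlation 0.7 within an instrument over time and 0.5 across instruments. The entries are the percentage of runs rejecting at follow-up.

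| Scaling | Neither declines | Ambulatory only, 0.3 SD | Clinic only, 0.3 SD | Both, 0.3 SD |
|---|---|---|---|---|
| Raw levels | 100 | 100 | 100 | 100 |
| Levels, z-scored within visit, aligned | 0 | 0 | 0 | 0 |
| Levels, z-scored to T1, not aligned | 0 | 40.7 | 43.6 | 100 |
| Levels, z-scored to T1, aligned | 1.8 | 93.2 | 94.1 | 1.8 |
| Paired change in T1 SD units, aligned | 1.1 | 89.6 | 90.3 | 1.4 |

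At T1, raw levels reject in 100% of runs and every z-scored version in 0%, because the z-scores are centred there by construction.

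**5. Why change is preferable to T1-anchored levels.** The levels version treats the T1 mean as fixed. Under the assumed correlations, the paired difference in levels has variance 1 + 1 − 2 × 0.5 = 1. The difference in changes has variance 2(1 − 0.7) + 2(1 − 0.7) = 1.2, since the cross-instrument terms cancel, and this governs how the mean really varies. The effective critical value is 2.576 / √1.2 = 2.35, which gives a two-sided error of about 1.9% against a nominal 1%. That agrees with the simulated 1.8%. The change version avoids this.

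**The case against.** The strongest reply is that Aim 1 does not rest on this test. Sample Size Analyses frames the aim as finding decline that clinic tests miss, and sizes the study for the proportion test. The article never calls the Wilcoxon test primary; it only comes first in order. If it were deleted, three analyses that use change would remain. This stands, and it limits the point to one test.

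Those analyses do not make the test harmless, however. The mixed models are fitted to each measure, with an expectation of larger ambulatory time effects but no stated between-instrument test. The proportion test is against zero and does not weigh ambulatory-only decline against clinic-only decline. The paired category comparison does contrast instruments on change, but it is labelled an additional sensitivity test.

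The second reply is that scaling and direction belong in a fuller plan. Units of recording are not necessarily units of analysis, and ambulatory data are scored before they reach the lead site. That also has force: nothing says that the investigators would subtract raw scores, and scores anchored to T1 and aligned would be informative at T2 and T3. But the article itself fixes what is compared (scores) and when (at each time point, hence also at T1). Moving from levels to change alters the analysis and is more than a scaling detail.

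**Conclusion.** The point holds for the Wilcoxon test only. As worded, it compares levels across instruments visit by visit and does not address sensitivity to change. This follows from the text and needs no assumption. The T1 comparison is uninformative about change whatever the scaling. On raw, non-overlapping scales the follow-up comparisons are too. The rejection rates rest on the assumed scales, correlations and normality; the p value of 3.3e-36 is a property of 210 same-sign pairs and carries no information about this trial.

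Three stronger readings are tempting, and the documents do not support them:

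- A reader might infer that Aim 1 lacks any analysis of change. Specific Aim 1 lists three.
- A reader might infer that the test must return either p near zero or a null. With T1-anchored, aligned scores it rejects in about 93% of runs when only one instrument declines, and in 1.8% when neither or both do.
- A reader might infer that the two sets of scores run in opposite directions. Slower reaction times and larger distances are worse, but the article gives no direction for the clinic tests. The conclusion does not need it.

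**What to change.** Restate the Wilcoxon test as a paired comparison of T1-to-T2 and T1-to-T3 changes. Orient each measure so that the same sign means decline. Divide by that measure's T1 SD, in line with the SD units already used for the decline categories. Name the ambulatory-clinic pairs within each cognitive domain in advance, and drop the T1 comparison as evidence on hypothesis 1.

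Optionally, add one joint mixed model on the standardised scores with a measure-by-time term, so that the expected larger ambulatory time effect is tested directly.

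The abstract's description of the test as a nonparametric t test is a clerical slip and should be brought into line with the Wilcoxon test named under Specific Aim 1.

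The cost is analysis wording only. No new data are needed, and the Results section says that data analysis had not started at submission.

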### Study Sample and Recruitment

The aim was to recruit 250 participants, with the expectation that 210 would also provide data at the final (2-year) follow-up. Participants were recruited through existing participant registries; electronic health record queries; institution-specific, participant-recruitment websites; clinic- and community-based recruitment; posting of flyers; and outreach to local partners, such as the local chapters of the National MS Society. Inclusion criteria (assessed by self-report) were (1) 18 years of age or older, (2) able to fluently converse and read in English, (3) MS diagnosis (confirmed via medical record review; all relapsing and progressive subtypes included), and (4) able to ambulate either independently or with the use of a cane or walker (or similar device) for at least 50% of the time at baseline; participants who lose ability to ambulate over the course of the study are retained, as this criteria only applies to initial enrollment. Exclusion criteria were (1) MS relapse within the past 30 days (may become eligible after 30 days; criteria used at T1, T2, and T3) and (2) inability to use study data collection tools (ie, ActiGraph wGT3X-BT [ActiGraph], smartphone app; volunteers “pass” this final exclusion criterion by independently completing a trial of the ambulatory assessment battery during the laboratory visit).

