### Sample Size Analyses

We conducted analyses to determine the sample size needed to address all study aims. The goal of the first study aim is to determine whether the ambulatory tests are able to detect cognitive decline from baseline (T1) to 1-year (T2) or 2-year follow-up (T3) for individuals where clinic-based tests do not detect decline. The proportion of participants who show no decline or improvement, absolute but subtle decline (change <1/2 SD), meaningful decline (change between 1/2 SD-1 SD) [71], or clinically significant decline (≥1 SD decline) [71,72] will be calculated for both ambulatory and clinic-based neurocognitive tests. For each cognitive domain, a binary variable will be created for each participant indicating whether the ambulatory and clinic-based cognitive measures are consistent with each other (eg, agree) about the degree of change or laboratory-based or ambulatory measures indicate a larger degree of decline. We will test whether the proportion of cases where ambulatory measures indicated a larger degree of decline (relative to clinic-based tests) is statistically different from 0; sample size analyses for this test indicate that a sample of 199 will have 95% power (with critical α=.01) to detect significance, where ambulatory cognitive tests show a greater level of decline compared to clinic-based tests in as few as 1.5% (n=3) of cases. This suggests that our expected final sample size of 210 has the power to detect even modest differences in analyses comparing proportions of the sample that show a decline on ambulatory cognitive tests but not on clinic-based tests.

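### The Aim 1 proportion test is set against a null of 0, so it does not compare ambulatory with clinic measures, and its 95% power is only the chance of seeing at least one case

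*Protocol article*

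**What the plan says.** The first hypothesis in the Introduction is comparative: "ambulatory measures of subjective and objective cognitive function will be more sensitive to longitudinal changes (over 2 years) in cognitive functioning compared to conventional clinic-based" testing. The long-term part of Specific Aim 2 confirms that Aim 1 is mainly about comparing the two kinds of test.

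Sample Size Analyses sorts each person's change into four bands: no decline or improvement, "absolute but subtle decline (change <1/2 SD), meaningful decline (change between 1/2 SD-1 SD"), and a decline of 1 SD or more. Then "a binary variable will be created for each participant indicating whether the ambulatory and clinic-based cognitive measures are consistent with each other (eg, agree") or one of the two shows the larger decline. The test is whether the share of people in whom "ambulatory measures indicated a larger degree of decline (relative to clinic-based tests) is statistically different from 0". Specific Aim 1 repeats the same null, asking whether the share of participants in whom "the ambulatory test indicates a greater degree of cognitive decline compared to the clinic-based cognitive tests is statistically different from 0".

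The power statement is that "a sample of 199 will have 95% power (with critical α=.01) to detect significance" when ambulatory tests show more decline than "clinic-based tests in as few as 1.5% (n=3) of cases". From this the section concludes that the expected final sample is enough even for modest differences. Study Sample and Recruitment gives that sample: recruitment is planned "with the expectation that 210 would also provide data at the final (2-year) follow-up".

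Specific Aim 1 lists three further analyses: Wilcoxon tests of ambulatory against clinic scores at each time point, sensitivity tests of paired differences in the four category proportions at 1 and 2 years, and a mixed model for each cognitive measure. No power is given for any of them.

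**The concern.** Showing that one method is more sensitive requires weighing cases where it shows more decline against cases where the other does. The stated test looks at one direction only and asks whether it ever occurs. Two imperfect tests will disagree in both directions even if nobody changes. The bands make this easy, because any fall below half an SD already counts as subtle decline, so a trivial difference around zero moves a person from one category to the next.

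At stake are the meaning of a significant result on this test and the assurance that the sample is large enough for Aim 1. The comparison variable is also called binary while its description has three states (agree, laboratory larger, ambulatory larger), so the article leaves unclear how direction is coded.

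**Working it through.** **1. The plan's own figure.** Inputs from Sample Size Analyses: n = 199, true proportion 0.015, power 95%, alpha .01.

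- P(at least one case) = 1 - (1 - 0.015)^199 = 1 - 0.985^199 = 0.9506.
- Smallest n reaching 95%: ln 0.05 / ln 0.985 = 198.2, so 199 (n = 198 gives 0.9498).
- The n = 3 in the text is the expected count, 199 × 0.015 = 2.985.

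Other readings do not give 95%. Requiring at least two cases gives 80.1%, and at least three gives 57.5%. A Wald test at alpha .01 gives 27.9% (one-sided) or 20.2% (two-sided). With a null of exactly 0, one case is impossible under the null, so the exact test rejects at the first case whatever alpha is. The figure of 199 is therefore the sample size for seeing one case.

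**2. What noise alone produces.** Assumptions: nobody truly changes, errors are normal and independent, baseline SD is 1, and cuts are at 0, -0.5 and -1 SD. With retest reliability r, the SD of change is √(2(1 - r)).

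Example with r = 0.80 for both measures: SD of change = √0.40 = 0.632. The shares with no decline, subtle, meaningful and clinically significant decline are 50.0%, 28.5%, 15.8% and 5.7%. By symmetry, P(ambulatory worse) = (1 - sum of squared shares)/2 = (1 - 0.360)/2 = 0.32, and the same for the clinic test.

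With clinic reliability 0.75-0.85 and ambulatory 0.75-0.95, ambulatory is worse in about 26-34% and clinic in about 30-36%. Even at 26%, P(no case in 199) = 0.74^199, about 10^-26.

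**3. When the truth is the reverse.** If the clinic measure truly declines 0.3 SD more and the ambulatory measure not at all, ambulatory still falls in the worse category in 6-26% of people at reliabilities of 0.70-0.97. The test then rejects with probability above 0.99999. At reliability 0.99 for both measures this falls to 82-89%.

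**4. What 210 pairs can detect in a two-directional test.** McNemar, two-sided .01, 95% power, discordant share π (assumed), difference d:

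n = [2.576√π + 1.645√(π - d²)]² / d²

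Check at π = 0.30, d = 0.157: (1.411 + 0.863)² / 0.0246 ≈ 210.

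| Discordant share (assumed) | Detectable difference, n = 210 |
|---|---|
| 20% | 13 points |
| 30% | 16 points |
| 40% | 18 points |
| 60% | 22 points |

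Three discordant cases against none gives a sign-test p of 2 × 0.5³ = 0.25. At least 8 against 0 are needed for p < .01 (2 × 0.5⁸ = 0.0078).

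**5. A plain paired test is not enough.** With no true change, ambulatory reliability 0.95 and clinic 0.75, the four shares are 50.0/44.3/5.6/0.1% and 50.0/26.0/16.1/7.9%.

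- Ambulatory worse: 0.443 × 0.500 + 0.056 × 0.760 + 0.001 × 0.921 ≈ 0.265.
- Clinic worse: 0.260 × 0.500 + 0.161 × 0.943 + 0.079 × 0.999 ≈ 0.36.

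McNemar with 210 pairs at two-sided .01 then rejects about 20% of the time, in favour of the noisier clinic test. At 0.95 and 0.80 it is about 14%. With ambulatory 0.75 and clinic 0.85 the tilt reverses (33.8% against 30.2%).

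**The case against.** The test against 0 is not the whole of Aim 1. Specific Aim 1 also plans paired differences in category proportions, in which clinic decline does count against ambulatory decline, and per-measure mixed models with an expectation of larger ambulatory time effects, which could fail. This stands, and it limits the point. A reader might infer that clinic-larger cases are never weighed, or that the first hypothesis would be declared supported whatever the data show. The article supports neither: the paired comparison is there, and no sentence makes the proportion test the sole decision rule.

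Those analyses still do not repair the problem. The paired comparison is ranked as a sensitivity test without stated power. The Wilcoxon tests compare scores at a time point, not change. The mixed models come with no stated formal contrast between measures.

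Rejection is also not literally certain. The reliabilities are assumptions, and under a stricter case definition (an ambulatory fall of at least half an SD with no clinic decline) the chance of any case drops to 0.02-0.11 at reliability 0.99 with equal true decline. Up to reliability 0.97 it stays at 0.85 or more.

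Finally, a condensed article may leave the coding of the binary variable to a fuller document, so a loss of direction is possible but not shown. The null of 0 is different: it is stated twice, and the sample size is derived from it. Aims 2 and 3 have their own calculation (214), so the study's overall size does not rest on this one.

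**Conclusion.** The point holds for the proportion test and its power statement. The test rejects on a single case and almost surely rejects from noise at assumed reliabilities of 0.75 to 0.95, so it cannot show that ambulatory measures are more sensitive. That one case disproves the null, and that 199 reproduces as the chance of at least one case (0.9506), depends on no assumption about reliability. The conclusion that 210 participants suffice for modest differences is unsupported: a two-directional paired test would need a gap of about 13 to 22 points for 95% power at 20% to 60% discordance, and the discordance rates are assumptions. The finding does not extend to all of Aim 1, where a comparative analysis exists but is given secondary rank and no stated power.

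**What to change.** 1. Drop the test of the ambulatory-larger proportion against 0 from both sections.
2. Code three outcomes per participant and domain: ambulatory larger, agree, clinic larger.
3. Make a comparison that uses both directions the main Aim 1 test at T2 and T3, reported as a difference with a confidence interval. Either a formal measure-by-time contrast on standardised scores, or a McNemar/sign test with decline categories set against each measure's own retest error, so that unequal reliability does not drive the result.
4. Replace the 199 / 1.5% / 95% sentence and the conclusion drawn from it with the detectable difference for 210 pairs over a range of discordance, as tabulated above if the paired test is chosen. A measure-by-time contrast would need its own calculation.

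The cost is rewording the Aim 1 analysis and sample size text, and a less favourable power statement. No new data are needed, and the Results section says analysis had not begun at submission.
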